##### Cluster-randomized trial of the implementation strategies

*Randomization*: For this cluster-randomized trial, we will randomize sites clustered within four VISNs to either REP or EBQI (Fig. 2). Two VISNs will implement virtual DPP and two VISNs will implement TLC. To ensure adequate number of pregnant women for ROSE, all four VISNs will have the option to implement ROSE for their pregnant patients. With our focus on increasing access to preventive services for women living in rural areas, sites that serve rural Veterans will be selectively recruited. Rural sites tend to be community-based outpatient clinics (CBOCs) as opposed to large VA medical centers (VAMCs), so at least one additional CBOC in each VISN will invited to participate. Because the same leadership team may oversee VAMC and CBOC operations, any VAMC and CBOC that share a leadership team will be randomized as a unit to avoid contamination across implementation strategies. Therefore, a total of 20 individual VA sites (VAMCs or CBOCs) will be included from four VISNs. With the balanced design, half of the sites (*N*=10) will receive REP and half will receive EBQI (*N*=10).

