
**Table ﻿2 Tab2:** Measures for Aim 2a

EBP	Primary outcome	Participation and engagement	Primary impact performance goals	Clinical outcomes and other VA performance measures
Virtual DPP	• # of eligible patients who register at the DPP site (i.e., enroll) • # of eligible patients who participate in virtual DPP and attend at least one session	• Average # of DPP sessions attended^a^ • Proportion who completed ≥3, ≥9 and ≥16 DPP sessions^a^ • Change in reported physical activity^a^ • % weight change at 12 and 24 months	Increase participation in weight management program (e.g., MOVE)	• Overweight/obesity/weight management • Prevalence of prediabetes, diabetes, and incident type 2 diabetes • HEDIS: Hypertension and Diabetes
TLC	• # of provider referrals for TLC • # of patients w/ TLC encounter (enrolled)	• Average # of TLC sessions completed^a^ • % with SMART goal^a^ • % with behavioral change (physical activity; diet: fruit, vegetable, and sugary beverage intake; stress and coping; and weight)^a^	Increase in telehealth encounters for prevention (e.g., Whole Health)	• Overweight/obesity/weight management • Prevalence of prediabetes, diabetes, and incident type 2 diabetes • HEDIS: Hypertension and Diabetes
ROSE [4]	• # of provider referrals for ROSE • # of patients w/ ROSE encounter (enrolled)	• Average # of ROSE sessions completed^a^ • Depression screening	Increase in telehealth care for mental health	• # of patients that return to VA post-partum (utilization of VA health services in the 12 months post-partum) • Mental health/depression

^a^This data will be collected as part of the EBP. All other data will come from CDW

We will include data on-site-, provider-, and patient-level variables from VA administrative data or our operations partners. For the sites, we will include facility type (VAMC or CBOC) and size, women panel size, proportion of women at site, type of comprehensive primary care model for women Veterans [4], number of designated women’s health providers, and urban/rurality. Provider characteristics will include provider type (MD or NP) and whether the provider is a designated women’s health provider. Patient-level controls will include sociodemographic characteristics, comorbidity including diabetes and cardiovascular risk, service-connected disability status, utilization, and the most common ICD-10 codes related to pregnancy status.

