*Data analysis plan for Aim 2a*: We will use generalized linear models to evaluate the effectiveness of the intervention strategies for implementation of the EBPs in increasing women’s participation in telehealth-based preventive care. The models will account for clustering at the site level as well as incorporating site- and patient-level covariates outlined above. The main outcomes will include the composite measures of the proportion of women referred and enrolled in preventive telehealth care services, and the primary independent variable of interest is implementation using REP versus EBQI. We will conduct subgroup analyses by EBP to examine if the effects of the implementation strategies on proportion referred and enrolled vary by EBP (TLC or virtual DPP) as well as evaluate the effect on the *primary impact performance metrics* for telehealth care (weight management programs, Whole Health, and telemental health). In each model, we will examine the potential moderating effects of site-level characteristics (e.g., facility type, size, women’s health care program model, etc.). Adjustment for clustering will be performed using Stata v15, and we will evaluate goodness-of-fit using Mallows statistic (Cp). For DPP and TLC, we will use appropriate generalized linear models to assess weight and behavior change and examine differences by levels of participation (number of sessions completed). For ROSE, we will assess depression scores by levels of participation.

*Power calculations*: We based power calculations on the study’s basic single level of clustering sample design, where sites are randomized to receive either REP or EBQI to implement the EBPs. To detect a moderate effect size in terms of Cohen’s *D* (.26 standard deviations) between REP and EBQI, with 20 sites, and cluster adjustment (ICC=.01) with 80% power we will recruit 40 women per site (total of 800 women). We have considered all 20 sites to be separate clusters in terms of these calculations.

Aims 2b–2d are summarized in Table 3.

**Table 3 Tab3:** Overview of Aims 2b–2d

Method	Timing (per QUERI Roadmap)			Intended analyses
	Pre-implementation	Implementation	Sustainment	
Site tracking log	• Meeting minutes • Templated reflections • Stages of Implementation Completion (SIC)			2b: SIC 2c: Adaptations, experiences of EBP implementation 2d: cost

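### Seven site-level covariates plus site-level moderators are too many for 20 randomised sites, and an EBP-specific model (about 10 sites) would keep 1 or 0 site-level degrees of freedom

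*Protocol article*

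**What the plan says.** All of this is in the protocol article.

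- **Covariates.** The text below Table 2 (Aim 2a: Measures) lists the site variables to be included: "facility type (VAMC or CBOC) and size, women panel size, proportion of women at site, type of comprehensive primary care model for women Veterans", then the number of designated women's health providers and urban/rural status. That is seven variables.
- **Model.** The data analysis plan for Aim 2a states: "The models will account for clustering at the site level as well as incorporating site- and patient-level covariates outlined above". It gives no cap and no selection rule.
- **Moderators and subgroups.** The same paragraph plans subgroup analyses by EBP (TLC or virtual DPP) and continues: "In each model, we will examine the potential moderating effects of site-level characteristics".
- **Fit.** It adds: "we will evaluate goodness-of-fit using Mallows statistic (Cp".
- **Clusters.** Under Randomization: "a total of 20 individual VA sites (VAMCs or CBOCs) will be included from four VISNs", and "Two VISNs will implement virtual DPP and two VISNs will implement TLC". Also, "any VAMC and CBOC that share a leadership team will be randomized as a unit". The number of such joint units is not given.
- **Power.** The calculation uses d = 0.26, 20 sites, 40 women per site, ICC 0.01 and 80% power. It treats all 20 sites as separate clusters and mentions no covariates.

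**The concern.** REP versus EBQI is a site-level contrast. Recruiting more women per site adds no degrees of freedom for it; only sites do. Each site-level covariate or interaction therefore spends from a budget of 20, or about 10 within one EBP. Spending most of it has two consequences. The strategy estimate loses precision through chance correlation between the covariates and the allocation. Also, standard errors that rely on a large number of clusters become too small. The covariates are probably correlated with each other as well, since the Randomization text says that rural sites tend to be CBOCs. At stake are the credibility of the primary comparison and whether the EBP-specific results can be interpreted at all.

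**Working it through.** **1. The plan's own power figure.** Design effect = 1 + (40 − 1) × 0.01 = 1.39. Effective n per arm = 400/1.39 = 287.8. Standard error of the difference in SD units = √(2 × 1.39/400) = 0.0834. For d = 0.26, assuming two-sided α = 0.05 (not stated), power is 87.7% by the normal formula and 83.9% by t on 18 df. The stated 80% is not reproduced exactly and is on the cautious side. The point here does not depend on it.

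**2. Residual site-level degrees of freedom.** Parameters = intercept (1) + strategy (1) + covariates (7, counting one parameter each) = 9. Residual df = sites − 9 − interactions.

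| Model | Sites | Residual df |
|---|---|---|
| Main | 20 | 20 − 9 = 11 (18 with no covariates) |
| One EBP | about 10 | 10 − 9 = 1 |
| One EBP, one moderator interaction | about 10 | 10 − 10 = 0 |

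A care-model variable with more than two categories, or sites randomised jointly, lowers each figure.

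**3. Loss of precision, whatever the variance estimator.** The variance of the strategy effect is multiplied by 1/(1 − R²), where R² is from regressing the allocation on the covariates. For k unrelated, normally distributed covariates and G sites, 1 − R² follows a Beta((G − 1 − k)/2, k/2) distribution.

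- G = 20, k = 7: Beta(6, 3.5), median 0.641, so the median inflation is 1/0.641 = 1.56. The mean is (G − 3)/(G − 3 − k) = 17/10 = 1.7.
- G = 10, k = 7: Beta(1, 3.5), median 1 − 0.5^(1/3.5) = 0.180, so the median inflation is about 5.5-fold (1/0.180 = 5.56). The mean is infinite.

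**4. Effect on power at 20 sites (d = 0.26).** Loss of df alone (11 instead of 18) takes 83.9% to about 81%. With the mean inflation of 1.7 and covariates that explain no site variance, power is about 59%.

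**5. Could the covariates pay for themselves?** With the plan's ICC and cluster size, the variance of a site mean is 0.01 + 0.99/40 = 0.03475, of which 0.01/0.03475 = 29% is between-site. Even covariates that explained all of it would leave 1.56 × (1 − 0.29) = 1.11 times the unadjusted variance, at the median. With larger denominators the between-site share grows. Assuming 300 eligible women and ICC 0.05, it is 0.05/(0.05 + 0.95/300) = 94%, and good covariates could then pay.

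**6. Type I error (simulated, no strategy effect, unrelated covariates, nominal 5%).**

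| Test | 20 sites, 7 covariates | 10 sites, 7 covariates |
|---|---|---|
| Uncorrected cluster-robust (t on G − 1, or normal) | 16-19% | 62-66% |
| Random intercept, normal reference; 40 women per site, ICC 0.01 | 6-9% | 7-10% |
| Random intercept, normal reference; 300 per site, ICC 0.05 (assumed) | 8-18% | 27-55% |
| Site-level t on residual df | about 5% | about 5% |

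The uncorrected cluster-robust test without covariates gave 5-7% at 20 sites and 6-11% at 10. A check with a binomial GLM, unequal site sizes and correlated covariates (normal reference) gave 18% and 69%.

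**The case against.** The strongest reply is that the protocol names software for the clustering adjustment but no variance estimator or small-sample correction, and an article may leave those to the SAP. This stands. A reader might infer that following the plan necessarily inflates the type I error. The documents do not support that: the last table above runs from about 5% to above 60% depending on a choice that is not stated. An uncorrected cluster-robust standard error is a natural reading of a GLM with clustering adjustment in Stata, but only a reading.

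Three other inferences also go too far.

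- That degrees of freedom are exhausted in the main model: 11 remain.
- That Mallows Cp will choose the covariates and so invalidate the p-value: the plan names it only for goodness of fit.
- That VISN is a randomisation stratum: sites are described as clustered within VISNs, but stratification is not stated in the text, and Fig. 2 is not shown.

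It can also be said that the EBP subgroup question could be answered by an interaction in the 20-site model, that moderators may be meant one at a time, and that the 10-site split is inferred. These are fair. But the text says moderators are examined in every model, and one interaction is enough to saturate a 10-site model.

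What the reply does not reach is the covariate list. Its entry into the models is stated, not omitted, and the loss of df and precision follows under any estimator.

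**Conclusion.** The concern holds as a defect of stated specification. Seven site covariates leave 11 site-level df in the main model and 1 in an EBP-specific model, or 0 with one moderator. If unrelated to outcome, they inflate the variance of the strategy effect by a median of about 1.56-fold (20 sites) or 5.5-fold (10 sites), a cost that the power calculation does not mention. Inflated type I error is conditional: serious with an uncorrected cluster-robust test, absent with a residual-df test, and in between for random-intercept tests according to ICC and cluster size. Separately, Mallows Cp is a least-squares criterion and is the wrong measure of fit for a clustered GLM of a proportion.

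The conclusion assumes one parameter per covariate, about 10 sites per EBP, 20 independent units (joint randomisation can only lower this), and, for the simulated figures, covariates unrelated to outcome.

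**What to change.** Amend the data analysis plan for Aim 2a as follows.

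- Limit the primary model to strategy plus one or two pre-specified site covariates, for example the site's pre-implementation rate of the relevant telehealth use from CDW. Add VISN only if randomisation was stratified by it.
- Name the inference: small-sample-corrected or permutation, on the units actually randomised. Trimming covariates alone is not enough, because four covariates with an uncorrected cluster-robust test at 20 sites still gave 11-13% in simulation.
- Move the remaining site covariates to sensitivity analyses.
- Test the EBP difference as a strategy-by-EBP term in the pooled model.
- Test moderators one at a time, labelled exploratory, in the pooled model only.
- Remove Mallows Cp.

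The cost is wording in the protocol and SAP, with no new data collection because the baseline rate would come from CDW. The downside is less adjustment for chance imbalance between sites in the primary model, which the sensitivity analyses cover.

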*Setting and site selection*: We recruited sites (Fig. 2 below) from the Women’s Health Practice-Based Research Network (PBRN), a network that provides a research infrastructure for investigators seeking to increase inclusion of women in VHA research or conduct multi-site women’s focused research in VHA. Comprised of approximately 70 VA sites that see one-half of women Veteran VA users, the PBRN helps investigators overcome the challenges of multi-site studies through the engagement of Site Leads with established working relationships with local clinicians and facility leadership. Sites were also recruited in collaboration with regional leadership in four regional Veterans Integrated Service Networks (VISNs). Each VISN was selected based on leadership’s interest in the EBPs, priorities for women Veterans’ preventive health, and our history of collaboration.

*Low-performing sites*: Our team has a long history of working with sites to improve women Veterans’ health, including QI efforts in low-performing sites. For the current project, a number of our sites are designated low-performing sites based on site visit assessment data.

*Patient eligibility and selection*: Women Veteran VA users are eligible for each EBP as follows: (1) *Virtual DPP*—overweight/obese women Veterans (BMI≥25 kg/m^2^ [≥23 if Asian]) with history of prediabetes (defined as either an HbA1c 5.7-6.5% or fasting blood glucose 100–125 mg/dL or oral glucose tolerance test 140–199 mg/dL) or history of gestational diabetes (GDM) or high risk on diabetes screening questionnaire. Women will receive invitation letters or be referred to the program by a healthcare provider and self-register with a CDC-recognized virtual DPP provider. (2) *TLC*—all women Veterans (who are not pregnant) are eligible to participate in TLC. Women will be referred to the program by a healthcare provider and will receive an outreach call from contracted health coaches to enroll. (3) *ROSE*—All pregnant women Veterans are eligible. Women will be identified and recruited by the site pregnancy/maternity care coordinator or other women’s health staff. As part of each implementation strategy (REP and EBQI, see below), sites will determine their own locally relevant recruitment strategies to engage 40 women Veterans/site in virtual DPP or TLC, and all interested pregnant women in ROSE.

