*Aim 2a: Measures*—These fall into four basic categories shown in Table 2. The *primary outcomes of interest* are access to and engagement in telehealth care for preventive services, measured by referrals and enrollment. We will create composite measures of the proportion of women who participate in preventive telehealth care services for each EBP (# participate/# eligible). The primary outcomes for virtual DPP include the number of women who self-register for DPP (i.e., enroll) and the number who participate in virtual DPP (i.e., complete at least one online DPP module). For TLC and ROSE, the primary outcomes include the number of provider referrals for the programs and number of women Veterans with enrollment encounters. Parallel encounter coding will be developed for ROSE with the guidance of our Office of Primary Care. *Participation and engagement* outcomes collected by EBP are based on the average number of sessions completed and behavior changes documented during the program (e.g., weight change, increase physical activity, depression screens). For virtual DPP, we will assess rates of participation and engagement according to CDC standards for DPP delivery (i.e., average number of sessions attended, proportion who completed ≥9 and ≥16 sessions, etc.). For TLC, rates of participation and engagement are at ≥3 calls and ≥8 calls based on guidance provided by VA national offices regarding meaningful levels of contact with this EBP. For ROSE, maternity care coordinators (or comparable role) and ROSE facilitators will collect data on the number of sessions completed and proportion of completion of postnatal depression screens among participants. The *primary impact performance goals* for the EBPs will be based on performance metrics for telehealth care. For virtual DPP, we will monitor site-level performance measures for participation in weight management programs (e.g., MOVE!). For TLC, we will monitor site-level changes in telehealth encounters for prevention (e.g., Whole Health). For ROSE, we will monitor site-level changes in the use of telemental health and site-level changes in number of prenatal referrals sent out of the VA. Across all EBPs, we will also monitor metrics for use of telehealth services by women Veterans living in rural areas. Secondary outcomes of interest will include *clinical outcomes and other VA performance measures* related to each EBP. For virtual DPP and TLC, we will examine trends in clinical outcomes including percent weight change over 12 and 24 months, prevalence of hypertension, pre-diabetes, and diabetes. We will also examine trends in incident type 2 diabetes (≥1 inpatient diagnosis or any combination of ≥2 within 24 months: A1C≥6.5%, or fasting glucose≥126, or random glucose ≥ 200 or 2-h 75-g oral glucose tolerance test ≥ 200, or outpatient diagnosis code, or anti-hyperglycemic medication claim except metformin) [38, 39]. The VA (HEDIS) performance measures for diabetes and hypertension focus on proportion with guideline-recommended level of control among patients with the condition. Although our project is focused on prevention, we will track these measures because EBPs focused on lifestyle behavior change could impact level of control among diabetics and patients with hypertension. For ROSE, we will examine trends in postpartum attrition from VA among pregnant women through utilization of VA health services in the 12 months post-partum.

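### Mallows Cp does not suit the clustered models for proportions in Aim 2a: it cannot show misfit of the full model and, in model comparison, is too lenient to site-level terms (minor)

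*Protocol article*

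**What the plan says.** All of this is in the protocol article under Aim 2.

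- **Model class** (Data analysis plan for Aim 2a): "We will use generalized linear models to evaluate the effectiveness of the intervention strategies".
- **Outcome** (same paragraph): "composite measures of the proportion of women referred and enrolled in preventive telehealth care services". Under Aim 2a: Measures, the denominator is the number eligible: "composite measures of the proportion of women who participate in preventive telehealth care services for each EBP (# participate/# eligible".
- **Clustering and covariates** (Data analysis plan for Aim 2a): "The models will account for clustering at the site level as well as incorporating site- and patient-level covariates outlined above". The text after Table 2 lists seven site-level covariates: facility type, facility size, women panel size, proportion of women, primary care model, number of designated women's health providers, and urban/rurality.
- **Moderators** (same paragraph as the model class): "In each model, we will examine the potential moderating effects of site-level characteristics".
- **Fit check** (same paragraph, in the sentence on clustering adjustment in Stata): "we will evaluate goodness-of-fit using Mallows statistic (Cp". The article names no larger reference model, no set of candidate models and no version of Cp for clustered or non-normal data.

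**The concern.** Cp was built for ordinary least squares with independent, constant-variance errors. The Aim 2a outcomes are proportions, whose variance depends on the mean, and women are clustered in sites. The statistic reflects neither feature, although the same paragraph promises an adjustment for clustering.

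Two uses are possible, and each has a problem. Read as a fit check on the full planned model, Cp is fixed by algebra and can never signal misfit. Read as a way to compare models, it counts every woman as an independent observation. Between-site variation alone can then make a site-level term look informative. This matters because strategy, the seven facility covariates and the proposed moderators all vary only between sites, and there are 20 sites. At stake are an uninformative fit check and, if moderators are judged by Cp, some site characteristics that appear to matter by chance.

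**Working it through.** **Inputs from the article.** 20 sites, 10 per strategy (Randomization); ICC .01 and 40 women per site (Power calculations). The article states no figure for Cp, so there is none to reproduce. The sample-size statement only lends its inputs. With two-sided alpha .05 assumed, its design effect of 1.39 leaves 400/1.39 = 287.8 effective women per arm and gives 84% (t, 18 df) to 88% (normal) power at d = .26. That is on the safe side of the stated 80% and does not bear on this point.

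**Assumptions.** Equal site sizes, and analysis at the level of the woman, which the patient-level covariates imply. The article does not give the number of eligible women per site, so sizes above 40 are assumed. Sizes above 40 are plausible because 40 is an engagement target while the denominator is eligible women; for TLC, "all women Veterans (who are not pregnant) are eligible to participate in TLC".

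**Step 1: the full model.** For a model with p parameters fitted to n women,

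Cp = SSE_p / s²_full − n + 2p.

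For the full model, SSE_full = (n − p)·s²_full. Hence

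Cp = (n − p) − n + 2p = p.

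The outcome data cancel. As a numerical check, a 12-parameter model fitted to 800 observations gave Cp = 12.000 when the model was right, when a strong quadratic term was omitted, when the outcome was pure noise, and under strong clustering.

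**Step 2: comparing models with and without one term.** Dropping one term changes Cp by F − 2, so Cp prefers to keep the term when F > 2. For a null site-level term, F computed as if women were independent behaves approximately as DE·χ²₁, where DE = 1 + (m − 1)·ICC and m is the number of women per site. Therefore

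P(keep a null site-level term) = P(χ²₁ > 2/DE).

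| Women per site (m) | ICC | DE | 2/DE | P(keep) |
|---|---|---|---|---|
| any | 0 | 1.00 | 2.00 | 16% |
| 40 (plan) | .01 (plan) | 1.39 | 1.44 | 23% |
| 200 (assumed) | .01 | 2.99 | 0.67 | 41% |
| 500 (assumed) | .01 | 5.99 | 0.33 | 56% |

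The probability reaches 50% when 2/DE equals the χ²₁ median of 0.455. That gives DE = 4.40 and m = 1 + 3.40/.01, or about 340 women per site.

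**Step 3: simulation check.** The set-up was 20 sites, a binary outcome with an assumed 30% event rate, and 12 parameters, six of them null site-level covariates. At ICC .01 a null site-level term was kept in 23.2% of 4,000 runs with 40 women per site, and in 42.7% of 1,000 runs with 200. A null patient-level term was kept in 15.1% and 13.9% of the same runs. The excess leniency is therefore specific to site-level terms.

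**The case against.** The strongest reply is that the plan gives Cp no role in building the primary model. It appears in one clause. The covariates are listed in advance, and strategy is named as the independent variable of interest. Cp = p for the full model is how the statistic is calibrated, and it is informative for submodels. A condensed article may also leave the reference model, candidate set and further diagnostics to a fuller document.

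Most of this stands, and it limits the consequence. A reader might infer that Cp will select covariates, could discard the strategy term, and so inflates the type I error of the REP-versus-EBQI comparison. The documents do not support that, because no selection by Cp is described.

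Nor can inflation be put down to Cp in general. In a simulation of 600 runs per setting (20 sites, assumed outcome mean .10, ICC .01, seven null site covariates, strategy forced in, cluster-robust t-test with 18 df), a true null was rejected as follows:

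| Model | 40 per site | 500 per site |
|---|---|---|
| All seven covariates fixed, no Cp | 16.8% | 13.5% |
| Covariates chosen by Cp | 14.8% | 15.8% |
| No covariates | 6.7% | 6.2% |

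With this test, the excess comes mostly from fitting seven site covariates on 20 sites, and it persists without Cp. With a site-level t-test, choice by Cp did matter (10–11% against 4–5%), but only if Cp selects.

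It is also right that at 40 women per site a single null site-level term is still dropped 77% of the time. Cp is too lenient there relative to independent data; it does not keep such terms more often than not.

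The reply does not remove the mismatch itself. The article names plain Mallows Cp for clustered models of proportions. That is a stated choice, not a detail left out.

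**Conclusion.** The point holds as a minor one. The named statistic does not suit the named models. Its inability to show misfit of the full model is exact algebra and needs no assumption. Its leniency to site-level terms is conditional on Cp being used to compare models. At the plan's own ICC and 40 women per site the shift is modest, 23% against 16%. The larger figures rest on assumed numbers of eligible women, and a larger ICC would act the same way (41% at an ICC of .05 and 40 per site). No effect on the primary estimate, its test or the sample size is shown.

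**What to change.** In the data analysis plan for Aim 2a, replace Mallows Cp with checks valid for clustered binomial models: observed versus predicted proportions by site and arm, site-level residuals, and an overdispersion check. If models or moderators are to be compared, name a criterion that respects the clustering, such as QIC for GEE or a marginal AIC with a site random effect. State that no fit statistic decides which terms stay in the primary REP-versus-EBQI model.

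The cost is a sentence or two of wording and a little extra routine analysis. No further data or participants are needed.
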